### Study Population

The study population includes individuals ≥18 years with an incident diagnosis of ACS during the study period 2006-2015, with at least two months of follow-up in the Information System for Research in Primary Care (SIDIAP) [12] after the index date. The next patients will be excluded: pregnant women on the index date; patients with a recorded diagnosis of ischaemic stroke in the six months prior to index date; patients living in a nursing home on the index date; and patients with Alzheimer’s disease or other dementias.

Case definition: patient with an incident diagnosis of ACS registered in CMBD-HA (dataset of diagnoses at hospital discharge) [13] of the Catalan Health Institute (ICS) within the period from 2006-2015. Index date definition: date of ACS episode.

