### Variables

#### Exposure Definition

Patients will be classified as “exposed” to the study drugs (antiplatelet agents, beta-blockers, ACEI or ARB, statins) if they are prescribed any of them after the episode of ACS (up to two months after the event). The dose prescribed in ECAP will be considered the daily dose used for the patient, and the number of tablets contained in each package will cover the same number of days (see drugs of study in Table 2).

**Table 1 table1:** International Classification of Diseases, Nineth Revision (ICD-9) codes for endpoints of study and procedures.

ICD-9 code	Description
411*	Unstable angina and other forms of acute coronary heart disease
410*	Acute myocardial infarction
433*, 434*, 435*, 436*, 437*	Ischaemic stroke
00.66, 36.03, 36.09, 39.50	Coronary angioplasty

**Table 2 table2:** Anatomical, therapeutic, chemical classification system (ATC) codes for drugs of interest.

ATC code		Description of therapeutic group

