#### Adherence Definition

To estimate medication adherence, we will calculate the PDC for all four study treatments during eight months of follow-up after the index date. The PDC calculation is based on the packages dispensed and days of supply for each package, considering that the number of tablets contained in one package covers the treatment necessary for 28 or 30 days, depending on the drug. The information will be obtained from the pharmacy invoice data. For the PDC calculation, the numerator is the number of packages dispensed (invoice register) during the first 8 months of follow-up, and the denominator is the period of 8 months, which is the period for the adherence measure. Based on the PDC, patient adherence to each study drug is usually classified into one of two categories using the standard threshold of 75% (≥75%: adherent, <75%: nonadherent) [6,9]. PDC=75% accounts for six packages (each one including one month of drug treatment) dispensed during eight months. We define adherent patients as those who have received at least six packages during the first eight months after the event. Finally, according to adherence to all four study drugs, patients will be classified as adherent if they get the refill for all study drugs: PDC antiplatelet ≥75% + PDC beta-blockers ≥75% + PDC ACEI/ARB ≥75% + PDC statin ≥75%.

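### Adherence is scored over a fixed eight months from the ACS date, although a study drug may be prescribed up to two months later, so the refill requirement depends on start date

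*Protocol article*

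**What the plan says.** Three sections of the protocol article bear on this point.

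- **Study Population** fixes time zero: "Index date definition: date of ACS episode".
- **Exposure Definition** counts patients as exposed to the study drugs "if they are prescribed any of them after the episode of ACS (up to two months after the event").
- **Adherence Definition** sets the measurement window: "we will calculate the PDC for all four study treatments during eight months of follow-up after the index date". For the ratio, "the numerator is the number of packages dispensed (invoice register) during the first 8 months of follow-up". This count is divided by a length of time that is the same for every patient and drug: "the denominator is the period of 8 months, which is the period for the adherence measure". Each drug is classified "using the standard threshold of 75% (≥75%: adherent, <75%: nonadherent"), which is then turned into a count: "PDC=75% accounts for six packages (each one including one month of drug treatment) dispensed during eight months". The operative rule is: "We define adherent patients as those who have received at least six packages during the first eight months after the event".

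A package is taken to last 28 or 30 days, depending on the drug. A patient is adherent overall only if the antiplatelet, beta-blocker, ACEI/ARB and statin each reach 75%. No section moves the start of the window to the first prescription or dispensing, and none shortens the denominator for a later start.

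**The concern.** The two definitions do not fit together. The first accepts a drug started at day 60 as a qualifying exposure. The second treats the 60 days before that start as days the patient failed to cover. Two patients who refill equally well after starting can therefore be labelled differently only because one was started later.

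This is the study's main exposure variable. It enters the Cox models for the composite endpoint, the comparison by number of drugs adhered to (objective 1), the analysis of factors related to adherence (objective 2) and the sick-leave comparison (objective 3). On the all-four definition, one late-started class is enough to make the patient nonadherent. In objective 2, a characteristic that goes with delayed starting would appear as a predictor of poor refilling.

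**Working it through.** **Inputs from the protocol article.** Window: eight months from the ACS. Latest qualifying prescription: two months. Threshold: 75%, expressed as six packages. Package length: 28 or 30 days. The length of a month in days is not given, so I use 240 days (8 × 30) and 243.5 days (8 × 365.25/12).

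**The plan's own figure.** 6/8 = 0.75, and 6 × 30/240 = 0.75. It reproduces for 30-day packages on 240 days.

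**Requirement by start day *s*, 240 days, 30-day packages.** Packages that fit = (240 − *s*)/30. Best attainable PDC = (240 − *s*)/240.

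| Start day | Days left | Packages that fit | Six packages as a share | Best attainable PDC |
|---|---|---|---|---|
| 0 | 240 | 8 | 75% | 100% |
| 30 | 210 | 7 | 85.7% | 87.5% |
| 45 | 195 | 6.5 | 92.3% | 81.3% |
| 60 | 180 | 6 | 100% | 75% |

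**Other ways of counting.**

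- Possible dispensings in 243.5 days (28- or 30-day packages): 9 from day 0 and 7 from day 60. Six packages are 6/9 = 67% and 6/7 = 86%.
- Days covered in 243.5 days: 0.75 × 243.5 = 182.6 days. From day 60 this is 182.6/183.5 = 99.5% of the days left.
- Six 28-day packages from day 60, 240 days: 168/180 = 93.3% of the days left.

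The size of the gap depends on the convention, but each one sets a higher bar for the later start.

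**Illustration with an assumed refill probability.** The document gives none, so a range is shown. Monthly refills are assumed independent. The entries are the chance of reaching six packages for one drug.

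| Monthly refill probability | Day 0 (6 of 8) | Month 1 (6 of 7) | Month 2 (6 of 6) |
|---|---|---|---|
| 0.75 | 0.679 | 0.445 | 0.178 |
| 0.85 | 0.895 | 0.717 | 0.377 |
| 0.95 | 0.994 | 0.956 | 0.735 |

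**What a start-based denominator changes** (75% of the days left, 240-day window, whole packages).

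- 30-day packages: five are enough once 0.75 × (240 − *s*) ≤ 150, that is, from day 40. A month-1 start needs 0.75 × 7 = 5.25, so still six. A month-2 start needs 0.75 × 6 = 4.5, so five.
- 28-day packages: a day-0 start needs 180/28 = 6.43, so seven. Six are enough once 0.75 × (240 − *s*) ≤ 168, that is, from day 16.

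**The case against.** Coverage of a common period, with initiation delay included, is a legitimate exposure. The Spanish ACS cohort described in the Introduction also used a fixed period, although it ran from hospital discharge. The operative rule is a count that leaves a prompt starter two packages of slack, so short delays matter little. Even a month-2 starter may average 180/5 = 36 days between 30-day packages and still collect six, against 240/5 = 48 days for a day-0 starter. Some patients counted as exposed may be continuing earlier therapy and have no delay. Objective 1 grades adherence by number of drugs, so one late class costs one step there.

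Most of this limits the size of the problem, and I accept it. It does not remove the inconsistency. The protocol never says that initiation delay is meant to count as nonadherence, and its two-month allowance points the other way. The 36-day against 48-day comparison itself shows unequal bars.

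Two stronger readings are tempting, and the document does not support either:

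- **That late starters in general must refill almost perfectly.** This holds only close to day 60 and mainly on the days-covered measure. Counted as dispensings in 243.5 days, the day-60 figure is 86%.
- **That the misclassification exaggerates the benefit of adherence.** This would need late starting to go with worse prognosis, which the document does not show. Placing diligent late starters among the nonadherent could equally dilute the contrast. The planned adjustment covers event type, angioplasty and comorbidity. Length of stay and time to first dispensing are not among the listed variables.

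**Conclusion.** The concern holds in limited form. The text fixes the ACS date as origin, eight months as denominator and six packages as threshold, while admitting drugs prescribed up to two months later. Under the plan's own one-month-package convention, the requirement rises from 6 of 8 to 6 of 6 between a day-0 and a day-60 start. The effect is graded: small for starts in the first days and largest near two months. The document does not say how many patients start late, so neither the amount of misclassification nor the direction of bias in the hazard ratio can be stated. The definition should be changed because it governs the main exposure and can be corrected at low cost from data already in use.

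**What to change.** For each drug first dispensed within the two-month window, compute PDC as the days supplied from first dispensing to the end of month eight, divided by the days in that interval. Apply the 75% threshold to that PDC. Fix the window in days, for example 240, so that six 30-day packages still equal 75% for a day-0 start. State how a drug not dispensed within two months is classified. Report time to first dispensing as its own variable. Keep the six-package rule counted from the index date as a sensitivity analysis, so that readers can see whether the result depends on start date. Starting the clock at discharge would not be enough, because a prescribing delay after discharge would still count as uncovered time.

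The work is a change of denominator, using the pharmacy invoice data already planned for the PDC. There are three costs:

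- Observation length varies from about six to eight months.
- Because packages are whole, the bars become closer but not equal. With 30-day packages the required number falls only for starts from about day 40.
- A threshold in days asks users of 28-day packages who start at day 0 for seven packages instead of six. If the window were set at 243.5 days, day-0 users of 30-day packages would also need seven (182.6/30 = 6.09).

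### The rule of at least six packages in eight months does not equal PDC ≥75% for 28-day packages: six of them cover about 69–70% of the window

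*Protocol article*

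**What the plan says.** Everything at issue is in one paragraph, the Adherence Definition of the protocol article.

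- **Basis of the measure:** "The PDC calculation is based on the packages dispensed and days of supply for each package". The text adds that "the number of tablets contained in one package covers the treatment necessary for 28 or 30 days, depending on the drug".
- **Ratio:** "the numerator is the number of packages dispensed (invoice register) during the first 8 months of follow-up". This count is divided by an eight-month span, whose length in days is not given.
- **Threshold:** each study drug is classified "using the standard threshold of 75% (≥75%: adherent, <75%: nonadherent".
- **Equivalence:** "PDC=75% accounts for six packages (each one including one month of drug treatment) dispensed during eight months".
- **Package rule:** "We define adherent patients as those who have received at least six packages during the first eight months after the event".
- **Four-drug classification:** the paragraph closes by returning to PDC and requires all of "PDC antiplatelet ≥75% + PDC beta-blockers ≥75% + PDC ACEI/ARB ≥75% + PDC statin ≥75" (per cent).

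The Exposure Definition, earlier in the Methods, also converts tablets to days one for one.

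**The concern.** The paragraph gives two tests for the same status. One is a ratio of days, with the days taken from each package's supply. The other is a count of packages, with every package treated as one month. Having said that some packages hold 28 days and others 30, it makes no adjustment for the shorter ones when it equates six packages with 75%.

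If the tests disagree, two programmers working from this paragraph could derive different exposure variables from the same invoice data. Adherence is the exposure in the main objective. It also defines the groups in secondary objectives 1 and 3 and is the outcome in secondary objective 2. Full adherence requires all four drug groups to pass, so one drug group at the boundary can decide a patient's overall classification.

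**Working it through.** **Inputs from the Adherence Definition:** threshold 75%; 28 or 30 days per package; at least six packages; window of eight months.

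**Assumption:** the window is not stated in days. I use 240 days (8 × 30) and the calendar lengths that eight consecutive months can have, 242 to 245 days.

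**Step 1: the plan's own figure.** Counting each package as one month, 6 / 8 = 75.0%. In days this is 6 × 30 / 240 = 180 / 240 = 75.0%. The figure reproduces. With 28-day packages it reproduces only if a month is also set to 28 days: 6 × 28 / (8 × 28) = 168 / 224 = 75.0%.

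**Step 2: the same rule on days of supply.** Formula: PDC = 6 × days per package / days in the window.

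| Window (days) | Days needed for 75% | Six 28-day packages (168 days) | Six 30-day packages (180 days) |
|---|---|---|---|
| 240 | 180 | 70.0% | 75.0% |
| 242 | 181.5 | 69.4% | 74.4% |
| 243 | 182.25 | 69.1% | 74.1% |
| 244 | 183 | 68.9% | 73.8% |
| 245 | 183.75 | 68.6% | 73.5% |

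Six 28-day packages fall short of 75% for every window in the table, by 5.0 to 6.4 percentage points. In a 240-day window, 75% coverage leaves 240 − 180 = 60 days uncovered, while six 28-day packages leave 240 − 168 = 72.

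**Step 3: who changes status.** A patient with exactly six 28-day packages of a drug passes the package rule and fails the PDC rule. A patient with seven has 196 days, or 80.0% (245 days) to 81.7% (240 days), and passes both. A patient with five fails both. For a drug supplied only in 28-day packages, the disagreement is therefore confined to those with exactly six.

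**Step 4: would a seven-package rule repair it?** For 28-day packages it would set the effective cut-off at 80.0–81.7%, which is 5.0 to 6.7 points too strict. It replaces one dependence on package size with another.

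**The case against.** The strongest reply is that the paragraph sets its own convention: the numerator is a count of packages, the denominator is eight months, and a package is one month of treatment. On that reading six packages and PDC ≥75% are a single rule, the arithmetic is exact, and the closing four-drug requirement is consistent with it. This stands as far as the figure of 75% goes. It does not remove the conflict, because the convention works only by setting aside the 28/30-day distinction that the same paragraph makes part of the calculation. A count of packages is not a proportion of days covered when packages differ in length.

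It can also be said that a condensed article may leave derivation details to a fuller document. But this article does not leave the rule open. It states the rule twice, and the two statements differ.

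Several stronger readings are tempting, and the documents do not support them:

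- **That every objective is affected.** Secondary objectives 4 (prevalence of use) and 5 (posology) are descriptive and do not use the cut-off.
- **That adherence is not comparable across the four drug groups.** Package size is said to vary by drug, but nothing shows which groups use which size. Both sizes could be mixed within every group.
- **That 30-day packages fail too.** Six of them reach exactly 75.0% in a 240-day window. The shortfall to 73.5–74.4% appears only if calendar months are assumed.
- **That the hazard ratios are materially shifted.** On the four-drug classification, a patient changes status only if the other three groups also pass, and no distribution of package counts is given.

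**Conclusion.** The definition is wrong as written for 28-day packages. Six of them give 68.6–70.0% coverage, against a stated threshold of 75%, for windows of 240 to 245 days. The conclusion does not depend on which of those lengths is chosen. The two rules therefore classify a patient with exactly six 28-day packages of a drug differently, and under the package rule the effective cut-off depends on package size.

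The defect reaches the exposure in the main objective and the adherence variable in secondary objectives 1 to 3. How many patients would be reclassified, and what that would do to any hazard ratio, cannot be computed from the document. The point deserves correction because it concerns the study's main exposure and the repair is cheap, not because a large effect has been shown.

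**What to change.** Drop the six-package rule and the sentence equating it with 75%. Then state three things:

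1. The length of the adherence window in days, for example 240 or 243.
2. That covered days are computed from each dispensed package's own 28 or 30 days of supply.
3. That a patient is adherent to a drug group if covered days divided by window days is at least 0.75, with the four-drug classification built from these.

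Do not substitute a seven-package rule, for the reason shown in step 4 of the working.

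The choice of window should be deliberate. At 240 days, six 30-day packages (180 days) just meet the threshold. At 243 days the requirement is 182.25 days and they do not. It should be settled before adherence is linked to outcomes, so that the definition cannot be chosen in the light of results.

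The cost is a short text correction and a small change in derivation code. The measure already draws on pharmacy invoice data, so no new source is needed. Reported adherence will be slightly lower for drugs in 28-day packages and, if a calendar-length window is chosen, for those in 30-day packages as well.

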A large epidemiological study enrolled 7519 participants with established CVD from urban and rural communities in countries at various stages of economic development [10]. Use of antiplatelet drugs, beta-blockers, ACEI or ARB, and statins was assessed. Overall, 4421 (58.5%) individuals were not taking any of the four proven effective drugs, whereas 233 (3.1%) were taking all four drug types. Individuals recruited in high-income countries had had a CHD event or stroke a median of 6.0 years (interquartile range [IQR] 3.0–10.0) before inclusion. Although medication use increased in line with increase of country economic status, adherence rates in high-income countries were sparse too: 62.0% for antiplatelet drugs, 40.0% for beta-blockers, 49.8% for ACEI or ARB and 66.5% for statins.

A meta-analysis of randomised clinical trials assessed adherence to therapy comparing different dosing regimens in patients with chronic CVD.[11] The study showed that dosing regimens with once-daily administration, compared with two or more daily administrations, were associated with a significant 56% risk reduction of nonadherence to drug therapy (relative risk 0.44, 95% CI 0.35–0.54).

Due to the improvement of morbidity and mortality found with the quadruple drug therapy with antiplatelet, beta-blocker, ACEI or ARB, and statin in patients with established CVD, it is necessary to assess the long-term adherence to these drugs in the Catalan population and its relationship with cardiovascular events and mortality. Our hypothesis is patients with established CHD who adhere to drug therapy with the four recommended pharmacological groups have a lower risk of MACE and all-cause mortality compared with patients who do not adhere to drug therapy.

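### The all-four adherence class counts patients never prescribed one of the four groups as nonadherent, so its hazard ratio measures four-drug coverage rather than adherence alone

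*Protocol article*

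**What the plan says.** Adherence Definition sets the measure: "we will calculate the PDC for all four study treatments during eight months of follow-up after the index date". Each PDC counts the packages invoiced in that window. The divisor is the same for every patient and every group: "the denominator is the period of 8 months, which is the period for the adherence measure". Six monthly packages out of eight meet the per-drug threshold of 75%. For the combined class, "patients will be classified as adherent if they get the refill for all study drugs", and the four thresholds are then listed jointly, so failing one means failing the class.

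Exposure Definition works differently. Patients count as exposed "if they are prescribed any of them after the episode of ACS"; the window for that prescription is two months. Study Population requires age 18 or over, incident ACS and at least two months of follow-up. It neither requires a prescription of each group nor excludes patients for a contraindication.

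The hypothesis at the end of the Introduction is that those "who adhere to drug therapy with the four recommended pharmacological groups have a lower risk of MACE". Death from any cause is named beside it, and the comparison is with patients who are not adherent. Secondary objective 1 grades patients by the number of drugs they adhere to (four, three, two, one, none).

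**The concern.** Adherence is something a patient does with a treatment that has been prescribed. A rule that scores an unprescribed group as 0% also captures what the prescriber decided. After ACS, a group may be withheld for intolerance, contraindication or the patient's general condition, and these can affect prognosis in their own right.

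The conclusion that the article anticipates is that adherent patients have a lower risk. If part of the nonadherent class is there because a group was never prescribed, a hazard ratio below 1 could not be read as the benefit of refilling, and a hazard ratio near 1 could not be read as its absence. The label on the main result would not match what was compared.

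**Working it through.** **The plan's own figures.**
- Sample size: 3415 cases in three years (2009-2011), a 30% ICS share and a ten-year inclusion period give 3415 / 3 × 10 × 0.30 = 3415, which agrees with the stated 3400 or so.
- Threshold: 6 packages / 8 months = 75%, as stated.

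Neither figure is in dispute.

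**Applying the written rule to two patients.** PDC = monthly packages dispensed / 8.
- Patient A is prescribed three groups and collects everything: 8/8, 8/8, 8/8 and 0/8, that is 100%, 100%, 100% and 0%. The fourth is below 75%, so A is nonadherent.
- Patient B is prescribed four groups and collects nothing: 0% four times. B is nonadherent.

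Both fall in the same class. No other section sets the PDC as not applicable for an unprescribed group.

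**Does secondary objective 1 separate them?** In part. A goes into the three-drug level and B into the no-drug level. But Patient C, prescribed four groups and refilling only three, shares A's level. Not prescribed and prescribed but not refilled remain pooled.

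**Can the cited data size the problem?** No. In the Spanish cohort described in the Introduction, the percentages use the whole cohort as denominator: 3231/7462 = 43.3% for beta-blockers and 3388/7462 = 45.4% for ACEI/ARB. These do not distinguish non-prescription from non-refill. They show only that all-four adherence there could not exceed 43.3%. If that ceiling applied here, at least 3400 × (1 − 0.433) = about 1930 patients would be nonadherent, of unknown composition.

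**Illustration on assumed values.** Let *s* be the share not prescribed at least one group and *b* the share adherent to all four among those prescribed all four. The part of the nonadherent class that could never qualify is w = s / (1 − (1 − s)b). With b = 0.4 (assumed):
- s = 20%: 0.20 / 0.68 = 29%
- s = 30%: 0.30 / 0.72 = 42%
- s = 40%: 0.40 / 0.76 = 53%

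Now suppose that refilling has no effect and that unprescribed patients have *r* times the hazard of the others. The crude hazard ratio, adherent against nonadherent, is about 1 / (1 − w + w·r):
- r = 1.5: 0.87 (s = 20%), 0.83 (30%), 0.79 (40%)
- r = 0.8: 1 / (1 − 0.294 × 0.2) = 1.06 (s = 20%); 1 / (1 − 0.526 × 0.2) = 1.12 (s = 40%)

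The sign depends entirely on *r*, which the article does not give. These values are before covariate adjustment.

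**The case against.** Four arguments deserve weight.

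- **The coding is inferred.** No sentence says that unprescribed patients are nonadherent. Exposure Definition could be read group by group, and speaking of a refill presupposes a prescription. That reading is possible for the per-drug PDCs. It does not rescue the combined class, which still demands all four thresholds and states no prescription condition. The article also does not say that exposure governs entry to the contrast.
- **Coverage by the full regimen is a legitimate question.** The hypothesis names the four groups together, and one of the cited cohorts compares combination with no combination. This stands. It is why the all-comers contrast should be kept and relabelled rather than discarded.
- **Adjustment is planned.** Table 3 lists COPD, heart failure and chronic kidney disease, and Comorbidities and Clinical Parameters adds renal function, blood pressure, type of index event, angioplasty and the Charlson index. The Discussion commits to adjusted Cox models. This should reduce confounding. It cannot remove it all, since intolerance and contraindication are not listed, and it does not change who is in the nonadherent class.
- **Secondary objective 1 grades the classes.** It helps to the extent shown in the working, and no further.

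A reader might infer that the hazard ratio is necessarily biased towards benefit, or that a known 20% to 40% of patients, 680 to 1360 of 3400, cannot be adherent. The article supports neither. Non-prescription may also reflect milder disease, which would push the other way, and the shares are assumptions with no source in the article.

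**Conclusion.** The point holds on the text. With a fixed eight-month denominator, four joint thresholds and no prescription condition, patients never prescribed one group are nonadherent even if they refill everything they were given. The resulting hazard ratio describes being prescribed and collecting all four groups, which is not the adherence question as worded.

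The size and direction of any bias cannot be fixed from the article. Bias towards benefit is plausible if unprescribed patients have a worse prognosis and adjustment is incomplete. The 29% to 53% and the crude hazard ratios in the working rest on assumed prescribing, adherence and hazard values; they show sensitivity and are not estimates. Nor does the point make the all-four contrast among all comers invalid: it is a defensible measure of coverage under the wrong name. This is a worthwhile and cheap improvement.

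**What to change.** Data Collection and Data Sources states that GP prescriptions and the corresponding pharmacy invoices are both held, so no new data are needed.

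- For each group, and in secondary objective 1, code not prescribed within two months separately from prescribed with PDC below 75%.
- Estimate each per-drug hazard ratio among patients prescribed that group.
- Report the all-four contrast among patients prescribed all four groups alongside the contrast in all comers, and label the latter four-drug coverage rather than adherence.

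The cost is re-coding and one further set of models. The restricted analysis will be smaller by a number that the article does not allow one to state (on assumed shares of 20% to 40%, it would keep 2720 to 2040 of 3400), and it generalises only to patients prescribed all four groups. It also leaves some mixing in place: a drug withdrawn later by the prescriber still gives a PDC below 75%, and the write-up should say so.
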